## Abstract

**Background:**

The transition from adolescence to adulthood is a ‘high-risk’ period for weight gain in the general population. There is speculation that this may also be a risk period for adults with intellectual disabilities; however, there has been no research which has monitored change in health indicators. Since adults with intellectual disabilities have higher rates of obesity and engage in more sedentary behaviour and less physical activity than the general population, there is a need to understand more about the lifestyle behaviours of this population during the transition to adulthood. This protocol paper will provide details of the *moving on and feeling good* feasibility study, designed for young people with intellectual disabilities.

**Methods/design:**

A multi-point recruitment strategy will be used to recruit 30 participants with a mild-moderate level of intellectual disability. The aim of the feasibility study is to examine the feasibility of recruitment, participant retention and the measurement of relevant health behaviour outcomes. The study will assess the feasibility of monitoring weight, diet and physical activity levels in adolescents over a 12-month transitional period from school to adult life. This mixed method study will provide insight into the lives of young people with intellectual disabilities and will examine the use of Walker et al.’s social-ecological approach to promote self-determination specific to lifestyle behaviours, during this transition period. Baseline data will be collected during the final year of school, with follow-up data collection at 6 and 12 months. Anthropometric (weight, height, waist and hip circumference), objective physical activity measures (7-day accelerometer wear) and dietary and choice measures will be collected at each time point to assess the feasibility of measuring diet patterns, food frequency, physical activity and BMI. Furthermore, ten participants will be selected for short semi-structured scoping interviews at baseline and 12-month follow-up, to gain information on psychological, social and environmental factors which might affect behaviour change.

**Discussion:**

The outcomes from the feasibility study will aid the development and piloting of a sufficiently powered randomised controlled trial. This would allow us to evaluate the effectiveness and sustainability of a lifestyle behaviour intervention, over a 5-year transition period.

**Electronic supplementary material:**

The online version of this article (doi:10.1186/s40814-015-0044-9) contains supplementary material, which is available to authorized users.

## Background

Obesity is a major public health concern internationally [1], and there is clear evidence of the negative impact of obesity on health, with an increased risk of chronic health problems [2] and increased mortality [3]. The prevalence of obesity in adults with intellectual disabilities is significantly higher than in the general population [4, 5]. Research also suggests cardio-metabolic risk factors are prevalent in individuals with intellectual disabilities from adolescence [6], contributing to the higher disease burden for individuals with disabilities [7]. Therefore, the need to support adults with intellectual disabilities to make positive lifestyle behaviour changes, as a means to health improvement, has been recognised globally [8–11].

There is also evidence that suggests young people with intellectual disabilities have higher rates of obesity than typically developing young people. For example, a population-based study indicated that the prevalence of obesity in young adults with intellectual disabilities aged 16–24 was 28.1 %, compared to 10.5 % in a comparison sample of young adults, aged 16–24, who did not have intellectual disabilities (odds ratio = 3.37, 95 % CI 2.12, 5.37; Melville et al. [4]). The comparison BMI data used was from participants in a nationally representative household survey aged 16–24 and living in the same geographical area as the young adults with intellectual disabilities. However, the study did not examine whether the large difference in the obesity rates could be explained by differences in the samples, such as gender or socio-economic status. The prevention of obesity is a priority for health care and highlighted as important for young adults with intellectual disabilities internationally [8, 10, 12, 13].

Research suggests a range of factors may contribute to increased obesity rates, such as inherent biological and psychological vulnerabilities. For example, adults with intellectual disabilities have higher levels of depression than individuals without an intellectual disability (3.8 % [14] compared to 2.6 % [15]) and lower levels of health literacy. In addition, there is also evidence of social inequalities, such as economic disadvantage (e.g. greater material hardship, living in more deprived neighbourhoods, reduced community and social participation) [16]. While there is a growing body of research which suggests that adults with intellectual disabilities lead more sedentary and less physically active lifestyles than the general population [17–21], there is limited evidence about the lifestyle behaviours of young people with intellectual disabilities. Population-based studies from the general population suggests that the 5-year transitional period between adolescence and young adulthood is known to be a period of increased risk for the development of obesity [22], unhealthy diet and low physical activity levels [23]. Transitioning from school to adulthood may mean a young person is leaving behind a structured supportive environment for one that is less so. For young people with intellectual disabilities, this change in environment is likely to be more pronounced, with research suggesting up to 75 % adults with intellectual disabilities are underemployed or unemployed up to 3 years after leaving school [24]. This may result in more time spent sedentary at home, or in a residential setting. A recent systematic review highlights there has been no research to date which has monitored change in weight, or lifestyle behaviours relevant to health with this population [25]; it seems likely this transition would be a high-risk period for young people with intellectual disabilities to experience weight gain.

Peers are an important part of young people’s lives [26]; however, there are likely to be fewer opportunities for adults with intellectual disabilities to socialise in adulthood [27] which may also impact on opportunities to participate in physical activity or sport. In addition, families and carers play an important role in the lifestyle behaviours of an individual’s intellectual disabilities. Research has suggested that parents and carers’ own lack of motivation or time to be active can be a barrier to supporting an individual with intellectual disabilities to participate in physical activity [28]. Further, recent research [29] suggests that some paid carers and family members who were supporting individuals with intellectual disabilities to take part in a walking intervention rewarded walking and good behaviour with sweet treats and fizzy drinks. Therefore, the positive and negative influence that parents and carers’ have on an individual’s choice about (or lack of) diet and activity needs further examination.

A growing international literature base suggests that individuals with intellectual disabilities have low levels of self-determination [30–33]. As such, researchers have emphasised the need to consider how the environmental context of the lives of individuals with intellectual disabilities impacts on their self-determination [34, 35]. For example, a reluctance to tackle tasks independently means that parental support may have a positive impact on a young person’s confidence about participating in physical activities. Previous studies by the authors have also highlighted the need to take into account the context of the lives of people with intellectual disabilities when applying models of healthy lifestyle behaviours [36, 37]. Adding environmental mediators (e.g. the influence of the family, peers, school culture, work/college culture, area lived in, community, green space, opportunities for PA, autonomy over dietary and PA behaviours) to a self-determination model offers a more sophisticated theoretical framework for future weight gain prevention research. A key element of this feasibility study is therefore to identify relevant environmental factors acting as potential mediators on self-determination that inform our understanding of lifestyle behaviours and health, at the time of transition.

The health and wellbeing of young people with intellectual disabilities is an area of concern, and tackling the rising rates of obesity before adulthood could prevent the development of obesity-related diseases. Currently, there are no published intervention studies which aim to improve the lifestyle behaviours, health and wellbeing of young people with intellectual disabilities, as they transition into adulthood. This feasibility study is the first part of a larger body of work which will explore and monitor the lifestyle behaviours of young adults with intellectual disabilities, over the transition from school to adulthood. The aim of the feasibility study is to examine the feasibility of recruitment, participant retention and the measurement of relevant health behaviour outcomes. In addition, the work will explore the feasibility of applying an existing socio-ecological model of self-determination [35] specifically to lifestyle behaviours, over this transition period (see Fig. 1). This model identifies ‘person-specific’ and ‘ecological-specific’ variables that can affect levels of self-determination in this population. It also identifies ‘mediating’ variables which could impact on the efficacy of interventions, which promote self-determination. This feasibility study will explore the significance of these mediators in young people with intellectual disabilities’ lives by exploring levels of social effectiveness (friendships, recruiting social support networks, joining groups, managing one’s life and daily routines, etc.), social capital (networks of social ties, supports, relationships, trust, cooperation, affiliations) and social inclusion (societal acceptance of people with disabilities within school, work and community settings). Understanding more about these mediators could then be used to inform an intervention to promote self-determination for lifestyle behaviours in young adults with intellectual disabilities.

**Fig. 1 Fig1:**
[figure not shown]
Data collection points of feasibility study

The term transition is used variably, with some authors [38] suggesting it is a gradual process spanning adolescence, while others suggesting it has more to do with a specific transition in one’s life, e.g. from school to adolescence [39]. In this study, we are interested specifically in the change in the physical environment from school to work or adult life. This study will monitor participants over a period of 12 months, which will allow us to assess the feasibility of retaining participating in a study over this transition period. It is out with the scope of this small-scale study to follow up over a longer transition period. The outcomes from the feasibility study will aid the development and piloting of a sufficiently powered randomised controlled trial. This would allow us to evaluate the effectiveness and sustainability of a lifestyle behaviour intervention, over a 5-year transition period.

The Medical Research Council (MRC) guidelines for evaluating complex interventions [40] will be used as the basis for the body of work described above. In keeping with phases one and two of the MRC framework, this study proposes to examine the feasibility of recruitment, participant retention and the measurement of relevant outcomes. In addition, it will explore the applicability of focussing on self-determination constructs for a future intervention for the prevention of weight gain. The study will address the following research questions:What are the most effective routes for recruiting young adults with intellectual disabilities?What are the recruitment and retention rates during a 12-month longitudinal study of young adults with intellectual disabilities?Can lifestyle behaviour outcomes (weight, diet, physical activity) and self-determination be followed up over time and are any changes observed?What are the environmental mediators of self-determination that need to be considered in relation to lifestyle behaviours and health, at the time of transition?Are Dietary Instrument for Nutrition Education (DINE) and multiple recall questionnaires appropriate dietary measures for young adults with intellectual disabilities?

## Methods/design

Outcomes from a 12-month longitudinal data will address questions 1–3 (Fig. 2). To answer research question 4, a sub-sample of participants will be included in a nested study involving semi-structured interviews before and after leaving school. In addition, follow-up interviews with a sample of family members will be carried out at the 12-month follow-up visit.

**Fig. 2 Fig2:**
[figure not shown]
Socio-ecological model of self-determination

### Inclusion criteria

Participants will be invited to join the study if they are over 16 years of age and have a medical diagnosis of mild-moderate intellectual disability (individuals who have specific disorders of developmental delay, e.g. speech and language delay or dyslexia or autism spectrum disorder without an intellectual disability, will not be included in the study). In addition, individuals will be included if they are in their final year of school and are independently ambulatory. The researcher will ask the teachers to identify students who fit these criteria. The researcher will also send out information to parents which states the inclusion criteria for taking part in the study. Parents are asked to contact the researcher if they do not think their child meets the inclusion criteria. Individuals will be invited to take part in the research, following the procedure described below. Ethical approval has been granted by the University of Glasgow ethics committee.

### Recruitment procedure

Thirty young adults with intellectual disabilities will be invited to participate from several recruitment points. The proposed number of participants is based on recommendations from authors specialising in feasibility and pilot studies [41, 42]. The sample will introduce sufficient variance to examine the feasibility of a larger study and allow the identification of potential environmental mediators.

Researchers have identified the need for a recruitment strategy [36, 43, 44]. A strategy has been designed (Additional file 1) to guide the recruitment process, based on the framework provided by Foster et al. [43]. Recruitment will be carried out from December 2014 to June 2015. The authors have strong links with mainstream and additional support needs (ASN) schools and community groups for disabled people. ASN schools will be contacted first as the authors expect this will be the most successful recruitment point, based on the number of students who will meet the inclusion criteria. If the recruitment target of 30 pupils from ASN schools is not met (schools which are within 20 miles of a university), mainstream schools will then be targeted, followed by disability clubs.

Potential participants will be identified from these three sources and recruitment rates monitored to identify the most successful recruitment methods that could inform a future large-scale trial. If young people are interested in the study (based on an overview of the study provided by the researcher, teachers/club leader), they will be given an information pack which contains details of the study. Participants can signal interest in the study by informing the researcher verbally, or signing and returning a tear-off slip in the information pack and returning it to their teacher/club leader. The information sheets have been designed and piloted for individuals with mild-moderate intellectual disabilities. The researcher will also offer to read information sheets aloud. Schools/clubs will then be contacted to arrange a consent and baseline data visit.

The researcher will ensure all the participants have capacity to consent to the research by asking a variety of questions to ascertain that the participant understands what is being asked of them (e.g. Can you tell me what this study is about? Do you know what this belt (accelerometer) is for? Who decides if you want to take part? What do you do if you do not want to take part anymore?). If the researcher does not believe a participant fully understands the study, they will not be included in the study.

The researcher working with the young people is an experienced health psychologist who has worked with individuals with a range of intellectual disabilities. Therefore, she will ensure that the participants understand what is being asked of them, have the opportunity to ask any questions and can change their mind about participation at any point. The researcher will also ensure she is communicating clearly, using appropriate language for the level of intellectual disability and is patient and empathic in her interactions with the young people.

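### Mainstream schools and clubs are opened only if ASN schools fall short of 30, which conflicts with using all three sources to find the most effective recruitment route (research question 1)

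*Protocol article*

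**What the plan says.** The first research question, listed at the end of the Background of the protocol article, is comparative: "What are the most effective routes for recruiting young adults with intellectual disabilities". The abstract describes the approach as several recruitment points feeding one sample: "A multi-point recruitment strategy will be used to recruit 30 participants with a mild-moderate level of intellectual disability".

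The Recruitment procedure section then says two things.

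- **Order and condition.** "ASN schools will be contacted first as the authors expect this will be the most successful recruitment point", the reason given being the number of eligible students there. The next step is conditional: "If the recruitment target of 30 pupils from ASN schools is not met", then "mainstream schools will then be targeted, followed by disability clubs".
- **Use of the data.** "Potential participants will be identified from these three sources and recruitment rates monitored to identify the most successful recruitment methods", with the result offered as possible input to a later large trial.

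Recruitment has a single window, December 2014 to June 2015. The Inclusion criteria require pupils to be in their final year of school.

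**The concern.** Filling 30 places and comparing three routes are different goals, and the plan claims both. A stepwise rule that stops when the places are full serves the first goal. It serves the second only to the extent that the first route fails. Read literally, one section says that three sources will be used and also that two of them may never be opened.

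What is at stake is the answer to the first listed research question. A team planning the later trial could read a good ASN yield as evidence that ASN schools outperform the alternatives, although the alternatives had not been tried.

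**Working it through.** **The plan's own figure.** The target of 30 rests on published recommendations ("The proposed number of participants is based on recommendations from authors specialising in feasibility and pilot studies"), not on a calculation, so there is no figure to reproduce. The check is on the logic of the rule.

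**Step 1: places left for the later routes.** Inputs are the total of 30 and the conditional rule, both from Recruitment procedure. Places left for mainstream schools and clubs together = 30 − ASN yield.

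| ASN yield | Places left for the other two routes |
|---|---|
| 30 | 0 |
| 25 | 5 |
| 20 | 10 |
| 15 | 15 |
| 10 | 20 |

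**Step 2: ASN schools reach 30.** Under the rule, no mainstream school or club is approached. Uptake is consented ÷ approached. For those two routes it is 0 ÷ 0, which is undefined. Question 1 then has data on one route out of three.

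**Step 3: ASN schools fall short.** Each route that is opened does yield a rate. Those rates differ from the ASN rate in two ways besides the route itself:

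- they come later in a fixed seven-month window, nearer to the point at which final-year pupils leave school;
- they are collected against a remainder of places, not an open target.

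Head counts cannot be used for the ranking. Once ASN schools supply 15 or more, no later route can exceed them, because 30 − 15 = 15.

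**Step 4: what precision adds, and what it does not.** The documents give no uptake rate. As an illustration, assume equal true uptake of 50% and that mainstream schools take all remaining places. With both proportions at 0.5, the Newcombe 95% interval for the difference is ±√(h₁² + h₂²), where h is the Wilson half-width: h = 1.96·√(0.25/n + 1.96²/(4n²)) ÷ (1 + 1.96²/n).

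- ASN 25/50 against mainstream 5/10: h = 0.134 and 0.263, so √(0.0178 + 0.0694) = 0.30, or −30 to +30 points.
- ASN 20/40 against mainstream 10/20: h = 0.148 and 0.201, so 0.25, or −25 to +25 points.
- All routes opened together, 10/20 in each: √(2 × 0.201²) = 0.28, or −28 to +28 points.

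Over assumed uptakes of 30% to 70% and ASN yields of 15 to 25, the stepwise limits lie about 17 to 36 points from zero. Opening the routes together with 10 recruits each gives about 21 to 31 points. The intervals are wide either way because the sample is small. Opening routes together gives every route some data and removes the order problem, but it does not make the comparison precise.

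**The case against.** The strongest case for the plan is that ASN-first recruitment is a sensible way to fill 30 places in a small study, and the article gives a practical reason for it. The article promises only to monitor rates; it promises no test and no interval. Questions 2 to 5 do not depend on comparing routes. Opening sites with fewer eligible pupils also spreads the effort of a researcher who already makes an average of two visits per participant at each stage. All of this stands, and it limits how serious the point is.

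Several stronger readings are tempting but are not supported.

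- *Question 1 cannot be answered at all.* This is literally true only if ASN schools fill all 30 places. Otherwise a descriptive rate is available for each opened route.
- *The order makes ASN schools the winner.* It can settle a ranking by head count. The article speaks of recruitment rates, and going first does not fix consented over approached, although timing may still distort it.
- *There is no date for switching routes.* The article refers to a recruitment strategy in Additional file 1, which is not shown. Switch dates and denominators may be there.
- *Small numbers show that the stepwise order is at fault.* A late route with 5 of 10 consenting would have a 95% Wilson interval of 24% to 76%, but that width comes from the small sample and would remain with routes opened together.
- *The result fixes the route of the later trial.* The article says only that it could inform that trial.

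None of this removes the conflict. The conditional rule is stated in the article itself, and a route that is never opened cannot be described.

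**Conclusion.** The point holds in a limited form. The conditional opening of routes conflicts with the statement that participants come from all three sources and with a comparative question 1.

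The gap is largest when the first route does best: at an ASN yield of 30, two of three routes have no rate. The authors expect ASN schools to be the most successful source; they do not say outright that these schools will supply all 30, so this is a scenario the plan leans towards and not a certainty. With a shortfall, the plan gives descriptive rates that cannot separate route from calendar time and remaining places. In neither case can it name the most successful route.

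This conclusion rests on the stated rule alone and not on the assumed uptake rates. It should be fixed. Recruitment is part of the study's aim and this is its first listed question, but rewording alone can cure it and the other questions are unaffected.

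**What to change.** Choose one of two changes to Recruitment procedure and to question 1.

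1. **Keep the comparison.** Approach at least a small, pre-set number of mainstream schools and disability clubs from the start of the December 2014 to June 2015 window, whatever the ASN yield. For each route report consented ÷ eligible pupils approached, with a 95% confidence interval, and call the comparison descriptive. Cost: some earlier contacts, for which the article says strong links already exist, and possibly slower filling of the 30 places. No extra participants are needed.
2. **Keep the stepwise order.** Drop the claim to identify the most successful route, and restate question 1 as the uptake rate in each route actually opened. Cost: wording only. The later trial then receives no evidence on unopened routes, and the report should say so.

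Under either option, the sentence about three sources should be reconciled with the conditional rule.
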